## Methods

### Study Design

This is a parallel randomized controlled trial with balanced randomization (1:1) conducted in 4 health centers in Sagnarigu municipality, Tamale, Ghana. An overview of the study design can be found in Textbox 1*.*

Study design.Recruitment of potential participantsEnrollment of eligible participantsInformed consent and baseline surveyRandom assignment into intervention and control groups:Kanvilli: 48 participants (intervention: n=24 [3 groups of 8]; control: n=24)Choggu: 48 participants (intervention: n=24 [3 groups of 8]; control: n=24)Kalpohin: 48 participants (intervention: n=24 [3 groups of 8]; control: n=24)Bagabaga: 48 participants (intervention: n=24 [3 groups of 8]; control: n=24)Focused Postpartum Care (Focused-PPC; intervention arm)Focused-PPC careFocus group discussions at endStandard postnatal care (control arm)Usual careNot applicableInterviewer administered surveys at certain time points (see Table 1) for both arms

**Table 1 table1:** Outcomes and evaluation.

Variables	Measurement	Baseline	1-2 weeks	6 weeks	3 months	6 months	12 months
Independent variables and potential covariates	Demographic questions, Obstetric history questions, Readiness for Hospital Discharge Scale – New Mother Form	✓					
Knowledge of postbirth warning signs	Investigator developed questions based on common postbirth complications	✓	✓		✓	✓	
Postpartum health behaviors	Specific questions assessing health behaviors will be tailored to the time frame post partum. Will include attendance to visits		✓	✓	✓	✓	✓
Postpartum health status	Edinburgh Postnatal Depression Scale, Perceived Stress Scale, Questions on complications experienced and other questions on health status as appropriate to the time frame after delivery, Measures of blood pressure, temperature, pulse, and weight	✓	✓	✓	✓	✓	✓
Feasibility, acceptability, and satisfaction	Focus groups with midwives and each group of participants in Focused-PPC^a^ intervention arm using focus group discussion guide						At exit

^a^Focused-PPC: Focused Postpartum Care.

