##### Postpartum Clinical Assessments

The clinical care component of the intervention follows the recommended clinical assessments by the GHS and the WHO and includes assessment of vital signs, fundal assessment, vaginal bleeding or discharge assessment, incision assessment, and a breast examination. After the 6-week postpartum time point, only vital signs are measured at each session. In sub-Saharan Africa, over 60% of maternal deaths occur within the vulnerable first year after birth [2]. Since maternal deaths extend far beyond the traditional 6-week time frame, it is important that quality clinical care extend to 1 after birth. Focused-PPC provides regular contact with and monitoring by a midwife for up to a year following birth.

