The primary outcome is knowledge of postbirth warning signs, measured through questions developed based on an evidence-based assessment of the most common postbirth complications. The secondary outcome is postpartum health behaviors, including specific questions assessing health behaviors tailored to the specific time frame postpartum. Other descriptive outcomes include postpartum health status, which will include measures of postpartum depression, stress, complications experienced, vital signs, and other questions on health status as appropriate to the time frame after delivery. Postpartum depression is measured through the Edinburgh Postnatal Depression Scale (EPDS), a self-report screening tool commonly used in perinatal settings [34,35]. The EPDS consists of 10 items assessing women’s depressive symptoms over the past week. The EPDS has a maximum score of 30, with higher scores indicating higher frequency and increased severity of depressive symptoms. Stress is measured through the Perceived Stress Scale (PSS), a 10-item scale assessing women’s stress levels over the last month [36]. The PSS evaluates a woman’s perceptions of unpredictability, lack of control, and overloading in her life, with a higher score indicating higher levels of perceived stress. The feasibility and acceptability of the intervention will be measured using end-project focus group discussion data obtained from midwives and participants in the intervention arm. Outcomes and time points of data collection can be found in Table 1.

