### Analysis Plan

Differences in outcomes between the intervention and control arms will be assessed. We expect that the intervention arm will have higher knowledge of postbirth warning signs than the control arm at every time point measured and that the intervention arm will have a larger increase in knowledge of postbirth warning signs between time points. We expect postpartum health behaviors to be different between the intervention and control arms.

All data will be reviewed for completeness and transferred to STATA (StataCorp) statistical software for analyses [37]. The primary variable of interest is knowledge of postbirth warning signs, measured on 4 occasions. The baseline measurement of knowledge of postbirth warning signs will be used in an initial *t* test to confirm that there is no difference in knowledge between the intervention and control arms before the study to validate the randomization procedure. We will model and test the difference between intervention and control arm knowledge of postbirth warning signs at each time point, and knowledge between time points will be assessed using a repeated measures multivariate ANOVA (MANOVA) with a time and treatment interaction as the primary analysis controlling for baseline demographic variables. For the intervention arm, follow-up secondary analyses will measure the change in postpartum health status, postpartum health behaviors, and clinical assessment data over time using repeated measures MANOVA. Ancillary analyses to be run between the intervention and control arms include a proportion test for the patient’s readiness for hospital discharge. Additionally, an evaluation of feasibility, acceptability, and satisfaction will be summarized for inclusion when discussing the cost or benefit of the intervention.

Using intent-to-treat, participants providing data at baseline and first check-in will be included. Missing data (eg, due to attrition) will be accounted for using multiple imputations via the mice package in R (R Core Team) [38]. Sensitivity to missing data will be assessed by comparing multiple imputations to complete case analyses.

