## Discussion

### Principal Findings

The purpose of this study is to implement and evaluate a postpartum care model entitled Focused-PPC in a parallel randomized controlled trial with 192 postpartum women at 4 health centers in Tamale, Ghana. Focused-PPC sessions are underway in all participating health facilities. The primary outcome is knowledge of post-birth warning signs. We expect that the Focused-PPC group will have higher knowledge of post-birth warning signs than the control group at every time point measured and that the Focused-PPC group will have a larger increase in knowledge of postbirth warning signs between time points. We are also measuring postpartum health behaviors such as eating a healthy diet, uptake of family planning, breastfeeding, and so on. We expect that more participants in the Focused-PPC groups will eat a balanced diet most days of the week and uptake family planning compared to participants in the control groups. Additionally, we also expect mental health outcomes such as positive depression screens to be significantly lower over time in the Focused-PPC group compared to the control group. Other descriptive outcomes include postpartum health status, and we expect to capture and treat blood pressure cases during the course of the study.

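### Repeated measures MANOVA is named for outcome families that include yes/no items; in the intervention arm it misstates the error rate, or cannot be computed, for rare items asked at five surveys

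*Protocol article*

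**What the plan says.** In the Protocol article, the Analysis Plan limits one sentence to the intervention arm and states there that "follow-up secondary analyses will measure the change in postpartum health status, postpartum health behaviors, and clinical assessment data over time using repeated measures MANOVA". Outside the knowledge analysis, the only other quantitative test named is between the arms: ancillary analyses "include a proportion test for the patient’s readiness for hospital discharge". The section also says that arm differences in outcomes will be assessed and that behaviors are expected to differ between arms, without naming a method for behaviors.

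The content of the three outcome families is described elsewhere:

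- **Health behaviors.** Data Collection or Measures says: "The secondary outcome is postpartum health behaviors, including specific questions assessing health behaviors tailored to the specific time frame postpartum". Table 1 adds "Will include attendance to visits" and schedules behaviors at five surveys (1-2 weeks, 6 weeks, 3, 6 and 12 months). Principal Findings says: "We expect that more participants in the Focused-PPC groups will eat a balanced diet most days of the week and uptake family planning", compared with control participants.
- **Health status.** This is classed as a descriptive outcome and includes "measures of postpartum depression, stress, complications experienced, vital signs, and other questions on health status". Principal Findings refers to depression as a positive screen.
- **Clinical assessments.** Postpartum Clinical Assessments lists vital signs and fundal, bleeding or discharge, incision and breast examinations, then says: "After the 6-week postpartum time point, only vital signs are measured at each session".

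**The concern.** Repeated measures MANOVA compares a vector of means over time and relies on those means being roughly multivariate normal. EPDS and PSS scores, blood pressure, pulse, temperature and weight suit it. A yes/no item is different in three ways.

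1. The natural summary is a proportion at each survey, and a multivariate F does not give one.
2. With few events the normal approximation fails, so the stated 5% is not the real error rate.
3. If two surveys have no events at all, the contrast between them is zero for every woman. The covariance matrix is then singular and there is no test.

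The method also needs the same measure at every occasion. Behavior questions are tailored to the time frame, so some items may not recur.

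At stake are p values for uncommon items that cannot be trusted or do not exist, and a change of method after the data are seen when the named one fails.

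**Working it through.** **Plan's own figure.** The article gives no event rate, power or sample size for these outcomes, so there is nothing to reproduce. The 192 was set for the knowledge score alone and is not affected.

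**Inputs from the article.**
- Intervention arm: 24 women at each of 4 centers, 24 × 4 = 96 (Study Design).
- Occasions: 5 surveys for behaviors (Table 1); sessions at 1-2 and 6 weeks only for examinations other than vital signs.
- Test level: 0.05 (Sample Size).

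**Assumptions, because the article gives no figure.**
- Item prevalence from 1% to 30%, constant over time (no true change).
- Latent within-woman correlation of 0 or 0.3.
- One item analysed at a time, no attrition, and no clustering by group of eight.

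**Test.** For T occasions, form the q = T − 1 successive differences for each woman, with mean vector d and covariance matrix S. Then T² = n d′S⁻¹d, and F = (n − q) / [q(n − 1)] × T² on q and n − q degrees of freedom. With n = 96 and T = 5, q = 4 and F = 92/(4 × 95) × T² on 4 and 92 degrees of freedom.

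**Check of the singular share by hand (independent surveys).** The chance e that a survey has no events is (1 − p)^96. The test fails when at least two of five surveys are empty: 1 − (1 − e)^5 − 5e(1 − e)^4.
- p = 2%: e = 0.144; 1 − 0.460 − 0.386 = about 0.15.
- p = 1%: e = 0.381; 1 − 0.091 − 0.280 = about 0.63.

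**Simulated results, five surveys, n = 96, nominal 5%.** Ranges cover both correlations and several independent runs of 4,000 to 6,000 trials per setting.

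| Assumed prevalence | Expected events per survey (96 × p) | No test possible | False positives when computable |
|---|---|---|---|
| 1% | 0.96 | 63-67% | far below nominal (0.7% at correlation 0.3) |
| 2% | 1.92 | 15-20% | 8-16% |
| 3% | 2.88 | a few percent | 11-18% |
| 5% | 4.8 | 0.2% (correlation 0.3) | 8-10% |
| 10% | 9.6 | none | 6-7% |
| 30% | 28.8 | none | about 5% |

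The error does not move one way. It is inflated between about 2% and 5%, peaks near 3%, and falls well below nominal at 1%, where most trials give no test.

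**Two occasions (examination findings).** There is no inflation: 3.9 to 4.4% at 2%, 3.9 to 4.0% at 5%, and 4.5 to 5.7% from 10% upward (correlation 0.3). What remains is non-computability at about 1% (16% of trials) and a conservative test there (1.6%).

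**The case against.** The other side has substantial points, and they set the limits of this one.

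- **A reader might infer that the whole secondary outcome gets wrong p values.** The documents do not support that. The named behaviors are diet, family planning uptake, breastfeeding and attendance. No rates are given, and nothing suggests they lie at 5% or below. At 10% or more the error is near nominal. Complications are the likeliest rare items, and they are called descriptive.
- **A reader might infer that MANOVA is why there is no estimate of how many more women adopt a behavior.** It is not. The MANOVA sentence concerns change within the intervention arm, whereas the expectation in Principal Findings is between arms. The article names no method for that comparison, and a condensed article may leave it to the full plan. If the same method were used on both arms, the error would be conservative at 1 to 3% prevalence (0.5 to 3.6%) and 4.4 to 5.0% at 5% or more.
- **A reader might infer that examination findings cannot be followed to 12 months as promised.** The Analysis Plan says only that change is measured over time, and two readings allow such a test. Table 1 does not list these findings as measures, so clinical assessment data may mean mainly vital signs, which suit the model.
- **Item formats are inferred.** Behaviors could be scored as counts or composites.

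What these objections leave is that the article itself fixes one continuous-data method for three families that, on its own description, include event-type items. That is a stated choice, not a detail left to an unseen plan.

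**Conclusion.** The point holds in a limited form. The within-arm method fits scores and vital signs but not yes/no items. For such an item asked at five surveys in 96 women, the nominal 5% test has about 8 to 17% false positives at 2 to 5% prevalence. It cannot be computed in about 15 to 20% of trials at 2% or about 63 to 67% at 1%. For common items the error rate is acceptable, and the remaining fault is that no proportion is estimated.

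The sizes rest on assumed prevalences and correlations, complete data, no group clustering and inferred yes/no formats. The choice of model, not the exact percentages, is what the article's text establishes.

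**What to change.** Amend the secondary-analysis wording before analysis:

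1. Keep the repeated measures model for continuous measures: EPDS and PSS scores, blood pressure, pulse, temperature and weight.
2. Analyse yes/no behaviors and complications that are asked at more than one survey with a logistic GEE or mixed model. Where events are few, use a small-sample or penalised method, or report counts only.
3. Include both arms with an arm-by-survey term. Control women complete the same surveys, and the Analysis Plan expects behaviors to differ between arms.
4. Report proportions with 95% CIs at each survey.
5. Report any fundal, bleeding or discharge, incision and breast findings that are recorded as counts at 1-2 and 6 weeks.

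This needs no new data and no change to the sample size or primary analysis. The cost is a change of wording and slightly more programming.

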### Randomization

Project assistants will meet with eligible participants after birth, at discharge, in a designated private spot at the health facility, where they will obtain consent and complete the baseline survey. After the baseline survey, participant allocation will be 1:1 for equal intervention and control sizes. Allocation will be completed according to a computer-generated list of random numbers, allocating group sizes of 8. The allocation will be generated by a data scientist on the research team. The data scientist will provide participant allocations (intervention arm or control arm) to the project team. Participants in the intervention arm will also receive a group allocation (allocated in groups of 8). Intervention arm group participants will then be contacted to begin their group postpartum care. There will be no blinding, as the study team will know which women are in the intervention arm (receiving Focused-PPC) and the control arm (receiving usual care).

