### Data Collection or Measures

In addition to the baseline survey, all participants will be given surveys at 1-2 weeks, 6 weeks, 3 months, 6 months, and 12 months from baseline. All surveys will be interviewer-administered by the project assistants and completed electronically via tablets using a secure database system. Strict procedures will be followed to protect participants’ confidentiality. We also plan to evaluate the feasibility, acceptability, and satisfaction of Focused-PPC. Focus Group Discussions will be conducted with the midwives who implemented Focused-PPC and with each group of participants enrolled in the Focused-PPC intervention arm after their 12-month sessions.

Independent variables and potential covariates will be measured through demographic and obstetric history questions and the Dagbani Readiness for Hospital Discharge Scale-New Mother Form (RHDS-NM). The RHDS-NM is a 22-item instrument that includes a self-reported rating scale with item scores ranging from 0 to 10 and possible scale scores ranging from 0 to 220 [32]. Higher scores indicate greater readiness for hospital discharge. The RHDS-NM, designed for use within English-speaking populations, was translated into Dagbani and adapted for use in Tamale. The Dagbani version of the RHDS-NM has demonstrated excellent reliability (Cronbach ɑ=.94) and measures postpartum mothers’ perceptions of readiness for discharge through examination of their personal status, knowledge, coping ability, and expected support [33].

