### Anticipated Limitations

Due to the nature of the study described in this protocol, the intervention is not blinded. There may be a potential for contamination since the midwives implementing the study are used in the health centers. However, since the study is not blinded, different midwives provide care and education to women during postpartum visits if they are in the control group to minimize contamination. In addition, the study is being conducted in one municipality in Tamale, so generalizability will be limited. We hope to conduct a larger study in the future. Given that the team in Ghana has worked in the setting since 2009 and has an established relationship with the health centers and women in the communities, we do not anticipate major recruitment difficulties. However, retention of participants and some participants missing scheduled sessions may be a challenge. We will engage participants and call them individually to remind them of upcoming sessions. We will ensure that midwives recap sessions are comprehensive enough to ensure knowledge transfer to those who missed previous sessions.

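### The analysis set labelled intent-to-treat leaves out randomised women without first check-in data, a condition met or failed only after randomisation

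*Protocol article*

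**What the plan says.** In the protocol article, the last paragraph of the Analysis Plan sets the population: "Using intent-to-treat, participants providing data at baseline and first check-in will be included". It continues: "Missing data (eg, due to attrition) will be accounted for using multiple imputations via the mice package in R", and names a comparison of imputed with complete-case results as the check on missing data.

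The order of events comes from two other sections. Randomization says: "After the baseline survey, participant allocation will be 1:1 for equal intervention and control sizes". Data Collection or Measures says that, besides the baseline survey, "all participants will be given surveys at 1-2 weeks, 6 weeks, 3 months, 6 months, and 12 months from baseline".

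On the primary outcome, the Analysis Plan says: "The primary variable of interest is knowledge of postbirth warning signs, measured on 4 occasions". Table 1 places these at baseline, 1-2 weeks, 3 months and 6 months. The primary analysis is the time-by-treatment interaction in a repeated measures MANOVA; arm differences at each time point are also to be tested.

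The Results section reports that all 192 women completed baseline and were randomised. No section brings excluded women back or describes an analysis of everyone randomised.

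**The concern.** An intention-to-treat comparison is protected because membership of the set is fixed at randomisation. Here every randomised woman already has baseline data, so the first half of the rule removes nobody. The second half does all the selecting, and it acts after allocation.

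Two things are at stake. First, a woman who misses only the 1-2 week survey would be dropped even though her scores at baseline, 3 months and 6 months exist. Second, if the chance of giving data at 1-2 weeks depends on arm, and the women who give none differ in knowledge, the retained arms are no longer comparable.

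The design makes such a difference plausible. On blinding, Randomization says: "There will be no blinding, as the study team will know which women are in the intervention arm". At 1-2 weeks only intervention women begin group sessions, and the Intervention Arm overview puts a project assistant at each session to gather the research data. Anticipated Limitations adds that "retention of participants and some participants missing scheduled sessions may be a challenge", and plans individual reminder calls for sessions.

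**Working it through.** **Step 1: when is the condition decided?**
- Baseline survey: before allocation (Randomization).
- Allocation: after baseline, 1:1, 24 per arm at each of 4 centres (Textbox 1), so 96 per arm and 192 in all.
- Next survey: 1-2 weeks (Data Collection; Table 1).

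The first check-in therefore falls after allocation. This holds even if the term means some later contact.

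**Step 2: what can be discarded?** Knowledge is measured on 4 occasions. A woman missing only the 1-2 week survey has 3 of the 4 scores observed. On the natural reading the rule removes all three.

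**Step 3: target difference.** Sample Size gives Cohen f = 0.15 and SD 1.4. For two equal arms the difference is 2 × f × SD = 2 × 0.15 × 1.4 = 0.42 points.

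**Step 4: illustrative bias at one time point.** Let dI and dC be the shares excluded in the intervention and control arms, and let excluded women score g SD below retained women in both arms. The mean of the retained women exceeds that of all women in an arm by d × g × 1.4, so

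bias in (intervention − control) = (dI − dC) × g × 1.4.

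All values of d and g are assumptions; the article gives none.

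| Loss in the two arms | g | Size of shift | Share of 0.42 |
|---|---|---|---|
| 15% and 5% | 0.25 | 0.10 × 0.25 × 1.4 = 0.035 | 8% |
| 15% and 5% | 0.5 | 0.10 × 0.5 × 1.4 = 0.07 | 17% |
| 15% and 5% | 1.0 | 0.10 × 1.0 × 1.4 = 0.14 | 33% |
| 10% and 10% | any | 0 | 0% |

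The sign depends on which arm loses more. If low scorers are lost mainly from control, the difference shrinks; if mainly from intervention, it grows.

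**Step 5: the primary interaction.** For a change from baseline to time t, the same reasoning gives (dI − dC) × (g at t − g at baseline) × 1.4. A constant deficit gives zero. A deficit that grows from 0.25 to 0.5 SD, with losses of 15% and 5%, gives 0.10 × 0.25 × 1.4 = 0.035 points.

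**Step 6: sample size and power.** The article's 192 assumes no attrition. It can be reproduced as a between-arm repeated-measures F test with 2 arms, 3 measurements and correlation 0.3: noncentrality = f² × N × 3 / (1 + 2 × 0.3) = 0.0225 × 192 × 3 / 1.6 = 8.1, power 0.808. The smallest N reaching 80% is 188, which rounds up to 192 in multiples of 64 (8 women × 2 arms × 4 centres). This is a reconstruction; the article states only 192.

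With an assumed 10% excluded overall (192 × 0.9 ≈ 173), power depends on the model:
- between-arm test, 2 arms: 0.808 to 0.766;
- time-by-arm interaction, 2 arms: 0.977 to 0.962;
- interaction with the 8 centre-by-arm subgroups: 0.789 to 0.731.

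**The case against.** Several stronger conclusions are tempting, and the article does not support them.

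- *The rule drops every woman who misses the first group session.* The rule turns on giving data, not on attendance. Surveys go to both arms, control women also have a visit due within 14 days, and nothing says that a woman absent from a session cannot be surveyed. The remark on retention concerns retention in general and missed sessions, not missed 1-2 week surveys.
- *The meaning of first check-in is settled.* It is not defined. If it meant whichever follow-up a woman gives first, women with 3- or 6-month data would stay in. The set would then be a common modified one, though still not all randomised women.
- *The bias is known to be material.* No loss rate or score deficit is given. Equal loss with an equal deficit gives zero, and a constant deficit largely cancels from the primary interaction.
- *The rule costs about four points of power.* That holds only for one reconstructed between-arm test. Full inclusion would not recover all of it, since women with baseline data alone add little information.
- *The rule contradicts the planned imputation.* Imputing later gaps within a restricted set is coherent. The better point is that the tool for keeping these women is already in the plan, although it relies on data being missing at random.
- *The article should have specified a mixed model or a missing-not-at-random analysis.* Such detail is commonly left to a statistical analysis plan, which is not at hand.

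These replies limit the size and certainty of the harm. They do not touch the core: a stated inclusion rule conditions on follow-up and is given the wrong label.

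**Conclusion.** The sentence is wrong as written. A set that requires first check-in data is a modified set defined after randomisation, and nothing elsewhere in the article corrects it. Read as the 1-2 week survey, it can discard observed primary-outcome data. It can also bias the arm comparison if response at that time differs by arm, which the design makes plausible and the article does not document.

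Neither the size nor the direction of bias can be determined. The range of 0.035 to 0.14 points applies to an arm difference at a single time point. It rests wholly on assumed losses of 15% and 5% and an assumed deficit of 0.25 to 1.0 SD, equal in both arms. It should not be read as an estimate, nor carried over to the interaction.

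The planned complete-case comparison cannot reveal the problem if both analyses start from the restricted set, because the excluded women appear in neither.

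**What to change.** Replace the sentence with a definition of the primary set as all 192 randomised women, each analysed in her allocated arm whatever follow-up she gave. Treat a missing first check-in as missing data under the multiple imputation already planned. Define first check-in. If the present rule is kept at all, keep it as a sensitivity set labelled modified intent-to-treat. The complete-case comparison would then start from all randomised women.

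The cost is one or two sentences and slightly more imputation work; enrolment and data collection do not change. Women with baseline data only will add little information, so the gain lies mainly in avoiding selection and keeping observed later scores. The article describes sessions as under way and reports no outcome results, so on its account the change can still be made before the outcome analysis.
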